#### Intervention group

2.4.4

*Single-cycle measurement and adjustment strategy.* In participants randomized to the intervention group, a single-cycle measurement and adjustment strategy will be applied. Participants will have their blood drawn as soon as possible after inclusion (but no earlier than 3 days after initiation of a DOAC) to measure a first peak DOAC level (2-4 hours after intake). The following scenarios can occur (Figure 2):(1)First peak DOAC level is within the on-therapy range → a second peak DOAC level will be measured 1 week later → the second peak DOAC level is again within the on-therapy range → no adjustment is necessary, and participant continues to follow-up.(2)First peak DOAC level is outside the on-therapy range → dose adjustment or switch to another DOAC if dose adjustment within an approved dose range is not possible → a new first peak DOAC level will be measured 1 week later, after which 1 of the 3 scenarios described will be reassessed. This process could potentially continue indefinitely; however, 2 primary rules will be applied—except in the case of rivaroxaban (Supplementary Figures), as literature indicates a higher incidence of bleeding complications are associated with its use. The 2 primary rules are as follows: (1) dosage adjustments are permitted only once, and (2) switching to an alternative DOAC is allowed only once. For each DOAC, including each specific dose, a Standard Operating Procedure (SOP) has been established (Supplementary Figures). These SOPs include a flowchart outlining the adjustments to be made based on specific DOAC levels.(3)First peak DOAC level is within the on-therapy range → a second peak DOAC level will be measured 1 week later → the second peak DOAC level is outside the on-therapy range → further DOAC management will be discussed in a multidisciplinary team consisting of experts in anticoagulant management.

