**Figure 2 fig2:**
[figure not shown]
Timeline of our single-cycle measurement and adjustment strategy. DOAC, direct oral anticoagulant; RCT, randomized controlled trial.

Based on the literature (Beers criteria [23]), we have specified apixaban and edoxaban as our first-choice DOACs in our SOPs. In circumstances in which initiating a participant on a DOAC is unsuccessful, ie, a participant has deviant DOAC levels after an adjustment has been made and after an individual treatment plan of the multidisciplinary team has failed, we will recommend the patient to switch to a VKA.

Importantly, in cases in which the DOAC level is not measurable or very low, we will first address therapy compliance with the participant, and a second DOAC level measurement will be performed before considering dose adjustment or switching to another DOAC.

*DOAC level measurement.* Blood sample analysis will be performed using commercially available and validated tests. For the measurement of DOAC levels, the following procedure will be followed. First, verification will be carried out to ensure that the DOAC was taken 2 to 4 hours prior to the blood sample collection. Blood will be drawn with minimal stasis in a 3.2% citrated vacuum tube (Becton Dickinson) via a puncture of the antecubital vein. Blood will be centrifuged in a 2-step procedure. First, it will be centrifuged for 5 minutes at 2500*g* at room temperature. For the second step, plasma will be centrifuged for 10 minutes at 10,000*g* at 18 °C. The Diluted TT Hemoclot test will be used for the measurement of dabigatran levels, and activated factor X (FXa) activity for the measurement of apixaban, rivaroxaban, and edoxaban levels (both Hyphen Biomed). More in detail, we will be using a clotting activity assay on the CS2500 Analyzer (Sysmex/Siemens), which employs a chromogenic substrate. This assay is the most widely used method globally to measure DOAC levels. It is ISO-15189 certified and registered under the In Vitro Diagnostic Regulation. This anti-FXa assay measures the effect of the DOAC and its active metabolites in relation to an excess FXa. The chromogenic substrate in the assay is cleaved by the residual FXa. Variations in active metabolites, which may be influenced by factors such as renal function disorders, are also assessed through this activity assay. Any shifts in the metabolite ratio will be reflected in the FXa activity measurement.

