#### Control group

2.4.5

In participants randomized to the control group, standard care will be given. Standard care includes that the choice of type and dose of DOAC are left at the discretion of the treating physician. There will be no interference in the choice or dose of DOAC at study inclusion. Further, it is up to the attending physician to follow guidelines on follow-up (renal function, body weight, etc.), but we assume this will at least include the annual check.

Additionally, in a subgroup of participants (all participants included in the MUMC+) blood samples will be collected at the time of inclusion and stored for future analyses.

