### Data analysis

2.5

After the first 100 patients in the intervention group have completed the single-cycle measurement and adjustment strategy, an analysis will be conducted to determine whether a second DOAC measurement is necessary, provided that the first DOAC measurement falls within the expected therapeutic range.

Baseline characteristics will be presented stratified by allocation. The primary analysis will be performed according to the intention-to-treat principle. In addition, a per-protocol analysis will be conducted. To evaluate whether the single-cycle measurement and adjustment strategy is superior to standard care with respect to the composite endpoint, a competing risks survival model according to Fine and Gray will be used to analyze time to first event, accounting for competing events. The effect of treatment will be expressed as hazard ratios with corresponding 95% CIs. The proportional subdistribution hazards assumption will be assessed using appropriate diagnostic methods. Recurrent events and their nature will be summarized descriptively. Depending on the distribution of event counts, additional analyses using Poisson regression may be performed to formally test differences in the number of events between groups.

Furthermore, the aforementioned analyses will also be conducted separately for new users and long-term users. In addition, subgroup analyses in participants aged > 70, > 80, and > 90 years will be performed. Last, participants requiring a switch to VKA will be excluded to perform subgroup analyses to evaluate the effect in participants who use a DOAC.

Two-sided *P* values < .05 will be regarded as statistically significant. Missing data will be imputed depending on the extent of missing data and the likely mechanism. Results will be expressed as odds/hazard ratios including 95% CIs.

Descriptive statistics will be used to present the prevalence of deviant DOAC levels. Logistic and linear regression analyses will be performed to estimate associations between potential predictors of deviant DOAC levels and actual levels (linear model) and a deviance indicator (logistic model). Mixed-effects regression models for repeated measures will be used to assess the effect of the intervention on quality of life over the course of follow-up. Fixed effects will be time, study group, their interaction, and a set of potential confounding variables.

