The feasibility and acceptability of the single-cycle measurement and adjustment strategy will be evaluated within a qualitative study. A cost–utility study will be performed to evaluate the cost-effectiveness of our intervention. Health care consumption will be collected from the EPRs and linked to Dutch unit costs. Kaplan–Meier survival curves will be used to visually represent the survival experience of participants in the 2 groups. To formally test differences in survival rates, Cox proportional hazards regression will be performed, adjusted for potential confounders (such as age, sex, and comorbidities).

Additional explorative analyses will be performed after stratification for eg, DOAC, new users vs experienced users, and adjustments due to DOAC peak plasma levels above and below the expected on-therapy range.

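### The analysis that drops participants needing a switch to VKA selects on a post-randomisation result produced only in the intervention arm, so it should not be read as a treatment effect

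*Protocol article*

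**What the plan says.** The protocol article makes intention to treat the primary analysis and adds a per-protocol analysis (2.5, Data analysis). It then lists subgroups by new versus long-term use and by age. The last item in that list is of another kind: "participants requiring a switch to VKA will be excluded to perform subgroup analyses to evaluate the effect in participants who use a DOAC".

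The need for a VKA switch is described only in 2.4.4, Intervention group, in the text after the Figure 2 caption. It arises when "a participant has deviant DOAC levels after an adjustment has been made and after an individual treatment plan of the multidisciplinary team has failed"; in that case "we will recommend the patient to switch to a VKA". The strategy containing this rule belongs to one arm: "In participants randomized to the intervention group, a single-cycle measurement and adjustment strategy will be applied".

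For controls, 2.4.5 says that "the choice of type and dose of DOAC are left at the discretion of the treating physician" and that "There will be no interference in the choice or dose of DOAC at study inclusion". No level-based rule, for VKA or anything else, is given for them.

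At its end, 2.5 also lists exploratory analyses stratified by, among other things, "adjustments due to DOAC peak plasma levels above and below the expected on-therapy range".

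**The concern.** Age and prior DOAC use are fixed before randomisation, so comparing arms within those subgroups keeps the protection of randomisation. Needing a VKA switch is found out afterwards, through the measurements that make up the intervention. Excluding on it removes from the intervention arm the participants in whom adjustment did not bring the level into range. Control participants who would have failed in the same way cannot be recognised, and they remain.

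The Introduction and Discussion treat deviant levels as associated with bleeding and thrombosis, the Discussion independently so. On that premise the removed group is at higher risk than average, and the remaining intervention participants would have fewer events than the full control arm even if measuring and adjusting achieved nothing. An effect in patients who stay on a DOAC is a figure that clinicians would quote. Section 2.5 sets a general two-sided 0.05 threshold and does not exempt this analysis from it.

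**Working it through.** **The plan's own figures.** For 15% versus 10%, and 20% versus 15%, with pooled variance, two-sided 0.05 and power 0.80, the two-proportion formula gives 685.6 and 905.4 per arm. The article states 686 and 905. Its totals follow as 2 × 686 × 1.10 = 1509 and 2 × 905 × 1.10 = 1991. The planning figures reproduce and are used below.

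**Inputs from the article.** Control yearly risk p is 15% or 20%, with n = 686 or 905 per arm (2.3). Follow-up is 2 years (2.4.7).

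**Inputs that are assumptions.** The article does not give the share s of each arm who would end in a VKA switch, or their hazard r relative to everyone else while on a DOAC. The Introduction reports deviant peak levels in 31% of outpatients and 40% of nursing home residents. That is the start of the pathway, not its end. I take s from 2% to 10% and r of 2 or 3.

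**Model under no true effect.** The would-be switchers are removed from the intervention arm and kept in the control arm. Hazards are constant, and competing deaths and drop-out are ignored.

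- Average hazard: λ = −ln(1 − p), which is 0.1625 at 15% and 0.2231 at 20%.
- Hazard of the others: λ0 = λ / (1 − s + s·r).
- Two-year event-free share, intervention: S_I = exp(−2λ0).
- Two-year event-free share, control: S_C = (1 − s)·exp(−2λ0) + s·exp(−2rλ0).
- Apparent hazard ratio: ln S_I / ln S_C.
- z = (S_I − S_C) / SE, with SE² = S_I(1 − S_I)/[n(1 − s)] + S_C(1 − S_C)/n.
- Two-sided false-positive rate: Φ(z − 1.96) + Φ(−z − 1.96).

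**One case in full** (p = 15%, n = 686, s = 10%, r = 2). λ0 = 0.1625/1.10 = 0.1477. S_I = 0.7442 and S_C = 0.7251, a difference of 1.9 points. The hazard ratio is ln 0.7442 / ln 0.7251 = 0.92. SE = 0.0245 and z = 0.78, so the false-positive rate is 0.119 + 0.003 = 12%.

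| Share excluded, relative hazard | HR, 15% yearly risk | 2-year difference (points) | False positives, 686 per arm | HR, 20% yearly risk | False positives, 905 per arm |
|---|---|---|---|---|---|
| 2%, twice | 0.98 | 0.4 | 5.3% | 0.98 | 5.5% |
| 5%, twice | 0.96 | 1.0 | 6.9% | 0.96 | 7.9% |
| 10%, twice | 0.92 | 1.9 | 12.2% | 0.92 | 16.3% |
| 10%, three times | 0.86 | 3.2 | 26.3% | 0.87 | 35.8% |

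With r = 1 the hazard ratio is 1.00. Keeping all randomised participants, or removing the same latent group from both arms, also gives 1.00 under this null.

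**What could change the direction.** A simpler one-year version uses risks in place of hazards: apparent risk ratio = 1/(1 − f + f·k), for share f with risk ratio k.

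- At f = 10% and k = 0.8 it is 1/0.98 = 1.02, the opposite direction.
- Suppose the exclusion also removes controls who move to VKA after an event, amounting to a fraction g of control events. The control risk p becomes p(1 − g)/(1 − g·p). At p = 15% and k = 2, this cancels the bias at g of about 6% for f = 5% and about 10% for f = 10%. Larger g reverses it.

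**The case against.** **The primary result is safe.** A reader might infer that the trial's main conclusion is biased. It is not. The primary analysis is by intention to treat, and 2.3 assigns the effect to the whole intervention group whatever the measurement leads to. The exclusion concerns one non-primary analysis, listed last. This stands and limits the severity.

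**The direction is conditional.** It is tempting to say that the analysis is biased in favour of the strategy without qualification. That needs excess risk among those who fail both an adjustment and a team plan. The article supports excess risk for deviant levels in general but gives no figure for this group. The exclusion sentence is also not limited to one arm. If controls who move to VKA in usual care are dropped as well, the pull may be offset or reversed. This stands too, but excluding controls after an event would be a second outcome-dependent selection and would not repair the first.

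**The size may be negligible.** The switch comes at the end of a long pathway, so a small share is plausible. At 2% and twice the hazard the distortion is trivial. The documents do not show that the share is that small.

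**VKA might be the safer drug.** The Discussion cites an odds ratio of 1.69 for bleeding when frail patients were moved from VKA to a DOAC. This does not rescue the analysis. Once the switchers are excluded, their risk on VKA no longer enters. The bias comes from their counterparts kept among the controls.

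**The adjustment strata.** A reader might take the exploratory stratification by adjustments above and below range as a second comparison of the same kind. The article does not say that the arms are compared within those strata, and describing the intervention arm fits its wording.

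**Conclusion.** The point holds as a should-fix. The exclusion conditions on a post-randomisation result whose only stated trigger exists in one arm, so the analysis is not a randomised estimate of the effect in DOAC users. On the trial's own premise that deviant levels raise risk, it would favour the strategy under no effect.

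The mechanism is certain; the size is not. The hazard ratios of 0.98 to 0.86 and the error rates of 5% to 36% rest on assumed shares and hazards, constant hazards and a normal approximation. The direction rests on excess risk among would-be switchers and on few control participants being excluded for a VKA switch in usual care.

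**What to change.** - Delete the exclusion as an estimate of treatment effect. Keep all randomised participants and count a VKA switch as part of the strategy, as the intention-to-treat analysis already does.
- Report the number, characteristics and outcomes of the switchers descriptively.
- If an analysis without switchers is kept, label it a non-randomised, descriptive sensitivity analysis with no significance claim. Show how its result varies with the assumed share and excess risk of would-be switchers in the control arm.
- State that the strata of adjustments above and below range are reported for the intervention arm only, without a between-arm comparison.

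Censoring at the switch with inverse-probability weights is an obvious alternative but would not remove this bias. Persistent deviance drives the switch. It is not systematically measured in controls, and in the intervention arm it leads by rule to a recommended switch. The samples stored at one centre (2.4.5) do not help either, because a single level at inclusion cannot identify deviance that persists after adjustment.

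The cost is a change of wording in the analysis plan, before outcome data are seen, and a short sensitivity table. It needs no new data or procedures. The trial gives up a headline effect in DOAC users.

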Nonetheless, only limited evidence is available for DOAC use in the frail older population because of their poor representation in major randomized controlled trials (RCTs). In fact, a Dutch RCT showed an increased risk of major bleeding without an efficacy benefit in frail older patients with AF switched from VKA to DOAC [5]. One explanation for this increased risk of bleeding is the altered pharmacokinetics of DOACs in this population. In a French observational study, a substantial proportion of older patients had DOAC-plasma levels outside the expected on-therapy range [6], an observation that was confirmed in our prior studies [7,8] and others [9,10]. For example, in our DOAC-FRAIL pilot study (*N* = 42) among frail older patients, a deviant DOAC peak plasma level, defined as “outside the expected on-therapy range,” was found in 54% of patients during acute hospitalization and in 31% at the outpatient clinic [8]. In addition, we found the same results in our DOAC-FRAIL nursing home study in which 40% of nursing home residents had a deviant DOAC peak plasma level (unpublished data). Continuing from these results, the recent study of Godino et al. [11] revealed marked associations between high DOAC-plasma levels and higher odds of bleeding and low DOAC-plasma levels and higher odds of thrombosis in a frail older cohort, which confirms previous study results [12,13]. With this in mind and considering the aging population and the subsequent increase in DOAC use among frail older patients, including nursing home residents, for whom guideline-based recommendations are lacking regarding the management of DOAC treatment, it is crucial to evaluate the efficacy and safety of DOAC use in this specific population. Therefore, more research is needed in the vulnerable older population to facilitate appropriate and safe DOAC use in this group.

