### Study design and objectives

2.1

The study is a 2-country, multicenter, prospective RCT. The primary objective is to evaluate the effect of a single-cycle measurement and dose adjustment strategy vs standard care. Specifically, we will investigate whether this strategy reduces the incidence of major and CRNM bleeding and thromboembolism in frail older patients (including nursing home residents). Secondary objectives are to investigate the feasibility of this single-cycle measurement and adjustment strategy, as well as the prevalence and determinants of deviant DOAC peak plasma levels in the frail older population, differences in quality of life, cost-effectiveness, and mortality between the intervention and control groups. Figure 1 shows the full timeline of the DOAC-FRAIL RCT in both arms.

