Dabigatran, apixaban, rivaroxaban, and edoxaban calibrators and assay controls will be obtained from Hyphen Biomed. All measurements will be performed according to the manufacturer’s instructions without modifications. Further, time from the last DOAC intake to time of blood draw will be recorded and, to interpret the DOAC level, we will use expected on-therapy ranges for peak plasma levels, defined as DOAC level measured within 2 to 4 hours after intake.

*Rationale for the use of DOAC peak plasma levels.* In the present study, we have opted to base our single-cycle measurement and adjustment strategy on DOAC peak plasma levels for several reasons. First, given our objective to reduce complications associated with DOAC use in the frail older population—who are particularly susceptible to bleeding risks, as shown by studies such as the FRAIL-AF trial [5]—deviant DOAC peak plasma levels are closely related to the risk of bleeding and thrombosis [11,12]. Second, as one of the primary advantages of DOACs is the absence of routine monitoring requirements, we sought to design a strategy that minimizes the need for intensive monitoring. As a result, we have chosen to measure only 1 DOAC level (peak), rather than both trough and peak plasma levels. This approach not only simplifies the strategy but also reduces the burden on patients, as it requires only a single blood sample. Finally, by limiting the strategy to peak-level measurement, we are able to reduce associated costs, further enhancing the feasibility of our strategy.

*DOAC peak-level interpretation.* For the DOAC peak-level interpretation, we will use the data (expected on-therapy ranges) recommended in the antithrombotic guidelines of the Federatie Medisch Specialisten in the Netherlands [24]. These expected on-therapy ranges are in line with data published by Douxfils et al. [25]. The Table shows the expected therapeutic ranges of peak DOAC levels as we will use them in the DOAC-FRAIL RCT.

**Table tbl1:** Expected on-therapy ranges of peak DOAC levels for atrial fibrillation and venous thromboembolism.

DOAC		Tmax (h)	Expected range	
			Lower limit (ng/mL)	Upper limit (ng/mL)
Apixaban, 5 mg	2 times daily	3-4	59	302
Apixaban, 2.5 mg	2 times daily	3-4	30	153
Edoxaban, 60 mg	1 time daily	1-2	125^a^	317^a^
Edoxaban, 30 mg	1 time daily	1-2	55^a^	225^a^
Rivaroxaban, 20 mg	1 time daily	2-4	177	361
Rivaroxaban, 15 mg	1 time daily	2-4	134^b^	278^b^
Rivaroxaban, 10 mg	1 time daily	2-4	91	195

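### The logistic model for determinants of deviant levels merges too-high and too-low levels in one indicator, so predictors that act in one direction are attenuated

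*Protocol article*

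**What the plan says.** Section 2.1 (Study design and objectives) lists among the secondary objectives "the prevalence and determinants of deviant DOAC peak plasma levels in the frail older population".

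Section 2.5 (Data analysis) names the outcome variables for that objective. The regressions concern "potential predictors of deviant DOAC levels and actual levels (linear model) and a deviance indicator (logistic model". There is thus one continuous outcome, the level itself, and one binary outcome.

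The Introduction defines a deviant peak level as one "outside the expected on-therapy range", which covers both sides. It gives prevalences without splitting them into high and low. In the pilot study a deviant level "was found in 54% of patients during acute hospitalization and in 31% at the outpatient clinic", and in the nursing home study "40% of nursing home residents had a deviant DOAC peak plasma level". The same section reports "associations between high DOAC-plasma levels and higher odds of bleeding and low DOAC-plasma levels and higher odds of thrombosis", so the two kinds of deviance carry opposite risks.

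The table of expected ranges in section 2.4.4 has nine drug-dose rows, each with its own limits. At the end of section 2.5 the article adds exploratory analyses stratified by, among others, type of DOAC and whether an adjustment followed a level above or below range.

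**The concern.** The Discussion names renal function, medication use, adherence and sampling time among the influences on the level. Factors of this kind can be expected to push a level mainly one way. Such a factor raises the odds of one kind of deviance and lowers the odds of the other. A yes/no indicator of any deviance then estimates only the net of two opposing effects, and the net depends on how common each kind is in the sample.

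At stake is what the secondary objective can tell a clinician. The logistic model could show little or no association for a factor that strongly predicts being above range and strongly protects against being below it. The result would also not transfer to a population with a different mix of high and low levels. A larger sample does not help, because the dilution lies in the outcome definition and not in the precision.

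**Working it through.** The article states no figure for this analysis. Its sample size concerns the composite endpoint and does not enter checks 1 to 3. Everything on effect sizes and on the high/low mix below is an assumption, shown over a range.

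**Check 1: multinomial model.** Let x be a standard normal predictor. Relative to in-range, the log odds of a high level are a_H − b·x and of a low level a_L + b·x. The pooled odds ratio is the one obtained when a binary logistic model is fitted to deviant yes/no. Population values by numerical integration:

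| Intercepts (high, low) | b | Prevalence high / low | True OR per SD, high / low | Pooled OR |
|---|---|---|---|---|
| −1.7, −1.7 | 0.5 | 14.6% / 14.6% | 0.61 / 1.65 | 1.00 |
| −1.7, −1.7 | 0.7 | 15.6% / 15.6% | 0.50 / 2.01 | 1.00 |
| −1.3, −2.0 | 0.6 | 21.1% / 11.2% | 0.55 / 1.82 | 0.845 |

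**Check 2: latent level tied to the article's prevalences.** Take a normal latent level with fixed lower and upper cut-offs. Set the cut-offs so that total deviance equals a documented prevalence π and a share f of it is high: upper cut-off z(1 − πf), lower cut-off z(π(1 − f)). A binary predictor shifts the level by 0.5 SD (assumption), placed at −0.25 without it and +0.25 with it.

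Example with π = 40% and f = 50%. The cut-offs are ±0.842.
- Without the predictor: P(high) = 1 − Φ(1.092) = 13.7% and P(low) = Φ(−0.592) = 27.7%, in total 41.4%.
- With the predictor: 27.7% and 13.7%, in total 41.4%.
- Pooled OR = 1.00. The OR for high (against not high) is (0.277/0.723)/(0.137/0.863) = 2.4, and for low 0.42.

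Pooled OR over the assumed high share:

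| π | f = 20% | 35% | 50% | 65% | 80% |
|---|---|---|---|---|---|
| 31% | 0.65 | 0.81 | 1.00 | 1.24 | 1.55 |
| 40% | 0.65 | 0.82 | 1.00 | 1.23 | 1.53 |
| 54% | 0.66 | 0.82 | 1.00 | 1.22 | 1.51 |

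At π = 40% the separate odds ratios hardly move over the same range of f: 2.3 to 2.8 for high and 0.36 to 0.44 for low. The pooled figure is therefore driven by the mix, while the separate figures are nearly stable.

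**Check 3: the linear model.** A level of 170 ng/mL is above range for apixaban 2.5 mg (30–153), within range for apixaban 5 mg (59–302) and below range for rivaroxaban 20 mg (177–361). An unscaled level therefore has no common meaning as deviance across the table.

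To see how far this could distort a crude comparison, assume a predictor that raises the level 25% at fixed dose. Assume 20% are on the lower dose without it and a share s with it. Use the range midpoints for apixaban, 180.5 and 91.5 ng/mL.
- Mean without the predictor: 0.8 × 180.5 + 0.2 × 91.5 = 162.7.
- Mean with it: 1.25 × [(1 − s) × 180.5 + s × 91.5], which is 170.0 at s = 50% (difference +7.3) and 136.6 at s = 80% (difference −26.1).

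For edoxaban the difference turns negative only at s = 80% (−9.6). For rivaroxaban 20/15 mg and dabigatran 150/110 mg it stays positive up to s = 80% (+16.8 and +11.8).

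**Check 4: events left after a split.** Levels are measured under the strategy in the intervention arm, planned at 686 to 905 participants. With 31% to 40% deviant, that is 0.31 × 686 ≈ 213 to 0.40 × 905 = 362 deviant first results. An even split leaves about 106 to 181 per side. An 80/20 split leaves about 43 to 72 on the rarer side.

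**The case against.** The strongest reply is that the indicator does not stand alone. The linear model keeps direction, so a factor that cancels in the logistic model need not disappear from the report. The exploratory analyses also distinguish adjustments made for high levels from those made for low levels. Both points stand and make the loss partial. Neither removes it. The exploratory split concerns adjustments and is not tied to the determinants models, and a mean difference in level does not say who falls outside their own range.

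A second reply is that near-complete cancellation needs a roughly even mix and mirrored effects, and the article gives no mix. This also stands. With one kind of deviance dominating, the pooled odds ratio is attenuated and not null.

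A third reply is that any out-of-range result matters in this strategy, so predicting any deviance is a legitimate question. It is, and this disposes of one tempting inference, that effects would be reported with the wrong sign. An odds ratio below 1 for a factor that raises levels is a true statement about any deviance when low levels are the commoner kind. It says little about mechanism, but it is not an error.

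A reader might also infer that the raw level would mainly reflect which drug and dose a patient was given. The article does not support that. It lists no predictors and does not exclude drug or dose, it gives no dose mix, and in check 3 the reversal appears only for two drugs at high assumed shares. Covariate lists, transformations and the choice of measurement may properly sit in the full protocol or SAP. The article does say that "time from the last DOAC intake to time of blood draw will be recorded", so sampling time is available to such a model.

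**Conclusion.** The point holds for the logistic outcome. The article itself fixes one two-sided indicator, so an analysis plan that follows it inherits the dilution. Its size cannot be known from the article. Under the assumptions in checks 1 and 2, the pooled odds ratio is 1.00 at an even mix with mirrored effects. It is about 0.845 at 21% high and 11% low, against true values of about 0.55 and 1.8. At 40% prevalence it ranges from 0.65 to 1.53 as the high share goes from 20% to 80%, while the separate odds ratios stay near 2.3–2.8 and 0.36–0.44.

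For the linear model only a clarification is warranted, because the article does not say how levels from nine drug-dose ranges are put on one scale.

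The weight is moderate: one secondary objective is affected, with partial mitigation already planned. The primary comparison and the sample size are untouched.

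**What to change.** Replace the single indicator with a three-category outcome (below, within, above the participant's own drug-dose range) in a multinomial logistic model. Two logistic models, below against in-range and above against in-range, would serve equally. The pooled indicator can stay as a summary of any deviance, labelled as such.

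As a supporting clarification, state that the linear model uses the level scaled to its own drug-dose range, or that it includes drug-by-dose terms.

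The cost is a change of wording before results exist, and no new data. The price is fewer events per outcome category (check 4). If one side proves rare, the number of predictors in that model has to be limited.
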